## Abstract

**Background:**

South Africa has the world’s largest HIV epidemic, but South African adolescent girls and young women (AGYW) acquire HIV at twice the rate of and seroconvert on average 5–7 years earlier than their male peers. Female caregivers (FC) are an untapped resource for HIV/STI prevention in South Africa and offer a novel opportunity to strengthen AGYW prevention efforts. This study will evaluate the effectiveness and cost-effectiveness of an evidence-based mother-daughter HIV/STI prevention program tested in the United States and adapted for South Africa, Informed Motivated Aware and Responsible Adolescents and Adults (IMARA), to decrease STI incident infections and increase HIV testing and counseling (HTC) and PrEP uptake in AGYW.

**Methods:**

This is a 2-arm individually randomized controlled trial comparing IMARA to a family-based control program matched in time and intensity with 525 15–19-year-old Black South African AGYW and their FC-dyads in Cape Town’s informal communities. AGYW will complete baseline, 6-, and 12-month assessments. Following randomization, AGYW-FC dyads will participate in a 2-day group workshop (total 10 h) that includes joint and separate mother and daughter activities. Primary outcomes are AGYW STI incidence, HTC uptake, and PrEP uptake at 6 months. Secondary outcomes are AGYW STI incidence, HTC uptake, and PrEP uptake at 12 months, sexual behavior (e.g., condom use, number of partners), HIV incidence, and ART/PrEP adherence and intervention cost-effectiveness. AGYW who test positive for a STI will receive free treatment at the study site. HIV positive participants will be referred to ART clinics.

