#### Primary outcomes

At 6-month follow-up, we will examine AGYW STI incidence (gonorrhea, chlamydia, and trichomoniasis), PrEP uptake and 1-month supply of medication, and HTC uptake.

Secondary Outcomes: At 12-month follow-up, we will examine AGYW STI incidence (gonorrhea, chlamydia, and trichomoniasis), PrEP prescription and 1-month supply of medication, and HTC uptake. At 6- and 12-month follow-up, we will assess AGYW sexual behavior (e.g., condom use, substance use during sex, number of partners, concurrent partners), using the AIDS Risk Behavior Assessment, [82] HIV incidence via HTC, and self-reported adherence to ART and PrEP (where appropriate) using Wilson’s 3-item scale [83]. We will use standard cost evaluation methods [84, 85] to assess IMARA-SA’s costs, including personnel time and non-personnel resources (e.g., travel expenses, snacks, incentives, curricular materials).

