### Statistical analysis

We will generate frequencies and summary statistics of predictor and outcome variables to screen and clean the data. We will evaluate randomization by comparing intervention groups on baseline variables using chi-square tests for categorical variables and t-tests or nonparametric Wilcoxon rank-sum tests for continuous variables. In subsequent analyses, we will adjust for predictor variables on which baseline randomization is not successful. We will examine if AGYW who complete the 6- and 12-month assessments differ systematically on baseline data from those lost to follow-up. We will examine correlations among the variables, inspect scale reliabilities to create appropriate scales, and create summary scores as appropriate (e.g., mental health problems). We will use models with random intercepts to account for clustering (if needed) and test the significance of clustering of subjects within groups.

We will analyze binary outcomes using logistic regression and continuous outcomes using linear regression. We will test the effect of the intervention on the primary and secondary outcomes and theoretical mediators, adjusting for confounders and the outcome at baseline as additional independent variables. Analyses combining time points will use generalized linear mixed-models with subject-specific random effects to account for correlation within repeated measurements. We will test an average effect across time points and effects on patterns of change from 6- to 12-months using interactions with time. Survival analysis methods will assess the effect of the intervention on incident STIs, using extended Cox regression models with fixed and time-varying covariates to estimate univariable and multivariable hazard ratios for associations of exposures with incident STI. Treatment effects may differ systematically depending on various factors, such mental health or substance use. We will test mediator and moderator effects according to Baron & Kenny [101] and Cohen & Cohen [102]. We will include interactions between treatment condition and covariates in the GLM, and obtain estimates for regression coefficients of the interaction terms, 95% confidence intervals, and *p*-values for the hypothesis tests.

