### Sample size calculation

Power analyses determined the sample size needed to compare the effect of IMARA-SA and control interventions on AGYW HIV/STI incidence and PrEP and HTC uptake. Because binary outcome variables pose the greatest challenge for power, we evaluated power for STI incidence (yes/no)—our primary outcome—across a range of prevalence estimates over 12-months. All calculations used a 2-sided test with alpha = .05. Based on data in the Plus Pills study, [103] using a Cox proportional hazards model with a range of incidence estimates, we will have ≥80% power to detect hazard ratios ≤0.5 for STI incidence ranging from 20 to 30%, even with 25% attrition. Effect sizes for binary outcomes is given in terms of the relative risk (RR), where RR = 1 indicates no treatment effect. A RR < 1 indicates a protective effect of the intervention. With 80% retention, we will have ≥80% power to detect RRs ≤ 0.38 when the proportion in the control group is 20%, and RRs ≤ 0.65 when the proportion in the control group is 50%. We also calculated the standard effect size (d) in standard deviations for group mean comparisons with 80% power for continuous outcomes, where d = 0 is defined as no treatment effect. We will be able to detect a small to medium effect size (d = 0.36) even with 75% retention. Low HIV incidence among AGYW (2.54%) per year will allow us to explore incidence, but we do not expect sufficient statistical power to test intervention effects on HIV incidence.

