### Data monitoring

Data will be monitored by Weststat on an annual basis. A designated monitor will visit the study site to review participant records, consent documents, source documentation, data collection instruments, screening/enrollment logs, visit checklists, baseline checklists, chart notes, referral forms, recruitment and outcome forms, participant evaluations forms, study blood draws, and survey data base entry. We will also assemble a Data Safety and Monitoring Board, which will review our activities to ensure participant safety and evaluate findings in an interim analysis of the data to determine if the RCT should continue or be stopped.

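### The protocol article names three primary outcomes at 6 months but sizes the trial on STI incidence alone over 12 months, at an undivided two-sided 0.05, and does not say which STI test decides

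*Protocol article*

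**What the plan says.** **Number and timing of primary outcomes.** The Abstract (Methods) lists three: "Primary outcomes are AGYW STI incidence, HTC uptake, and PrEP uptake at 6 months". The Primary outcomes section agrees: "At 6-month follow-up, we will examine AGYW STI incidence (gonorrhea, chlamydia, and trichomoniasis), PrEP uptake and 1-month supply of medication, and HTC uptake". Study objectives makes the same three comparisons at 6 months and places the 12-month comparisons among the secondary objectives.

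**Sizing.** The Sample size calculation opens by saying that power was examined for HIV/STI incidence and for PrEP and HTC uptake. It then says: "we evaluated power for STI incidence (yes/no)—our primary outcome—across a range of prevalence estimates over 12-months". The level is given once: "All calculations used a 2-sided test with alpha = .05". For STI, the claim is at least 80% power for hazard ratios of 0.5 or lower in a Cox model, at incidences of 20% to 30% and with 25% attrition. For binary outcomes in general, it gives detectable relative risks at control proportions of 20% and 50% with 80% retention.

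**Analysis.** Statistical analysis assigns logistic regression to binary outcomes and mixed models to analyses that combine time points. It adds: "Survival analysis methods will assess the effect of the intervention on incident STIs", using extended Cox regression. No STI analysis is named as primary.

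**The concern.** Two things are fixed inconsistently. First, a reader of the Abstract expects three primary tests at 6 months, while a reader of the sample size section expects one at 12 months. The outcome on which power was calculated is, by time point, the one listed as secondary. Second, the full 0.05 is used for each calculation although three outcomes carry primary status, and nothing says whether one, all, or a particular one must succeed.

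This affects what the trial may conclude. HIV testing and PrEP are taught directly in IMARA-SA (Table 1), while the control programme touches HIV prevention only briefly. Uptake could therefore move while infections do not. Whether that result would count as a positive trial cannot be settled from the article as written. The choice between logistic and Cox regression for STI is also open, and could be made after the results are seen.

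**Working it through.** **Inputs from the article:** 525 dyads, 1:1; 25% attrition; hazard ratio 0.5; STI incidence 20% to 30%; two-sided alpha 0.05; three outcomes called primary.

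**1. The plan's own STI figure.** Schoenfeld events for 80% power, 1:1: 4 × (z₁₋α/₂ + z₀.₈₀)² / (ln HR)².
- At 0.05: 4 × (1.960 + 0.842)² / 0.693² = 65.3, so 66 events.
- Participants analysed: 525 × 0.75 = 393.75.
- If 20% to 30% is the overall incidence, there are 78.75 to 118.1 events. Power = Φ(√events × 0.693/2 − 1.960) = 86.8% to 96.5%. The claim of at least 80% is reproduced.
- If 20% to 30% is the control-arm incidence, the intervention-arm incidence at HR 0.5 is 1 − √(1 − p), that is 10.6% to 16.3%. This gives 60.2 to 91.2 events and power of 76.7% to 91.2%, so the 20% end falls a little short. The article does not say which reading applies.

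**2. Familywise error with three tests at 0.05, if any one suffices.**
- Independent tests: 1 − 0.95³ = 0.143. The upper bound is 3 × 0.05 = 0.15.
- Correlated tests (simulation, 1,000,000 draws of three equally correlated normal statistics, each tested at |z| > 1.96):

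| Correlation | Familywise error |
|---|---|
| 0.3 | 13.6% |
| 0.5 | 12.6% |
| 0.8 | 9.8% |

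The correlations are assumptions; the article gives none. If all three outcomes had to succeed, or STI alone decided, testing three outcomes would add no inflation.

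**3. What a split would do to the stated power.** Bonferroni share: 0.05/3 = 0.0167, z = 2.394. Familywise error is then 1 − (1 − 0.0167)³ = 4.9% for independent tests.
- Events for HR 0.5: 4 × (2.394 + 0.842)² / 0.693² = 87.2, so 88.
- Power with 25% attrition, at incidences of 20% and 30%:

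| Incidence read as | Alpha 0.05 | Alpha 0.0167 |
|---|---|---|
| Overall | 86.8% to 96.5% | 75% to 91% |
| Control arm | 76.7% to 91.2% | 62% to 82% |

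- Binary outcomes, 525 × 0.80 / 2 = 210 per arm, alpha 0.0167, clustering ignored: 90.5% at RR 0.38 (20% control) and 89.8% at RR 0.65 (50% control). A split is affordable for the relative risks the article states. The strain is on STI at the low end.

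**4. The time point.** Fewer infections accrue by 6 months than by 12, so power for the 6-month comparison is lower than a 12-month calculation shows. The article gives no 6-month incidence. As an illustration only, assume that 20% to 30% is the overall 12-month incidence and that the hazard is constant. Six-month incidence is then 1 − √0.8 = 10.6% to 1 − √0.7 = 16.3%. That gives 41.6 to 64.3 events among 393.75 and power at 0.05 of about 61% to 79%.

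**5. Which STI test.** The mixed model is described for combined time points, so it does not compete for the 6-month comparison. Logistic and Cox regression remain. If they correlate at 0.7 to 0.95 (assumed), taking the better of the two would give 8.4% to 6.5% for a single outcome instead of 5%. That inflation is modest. The larger matter is that the deciding test is open.

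**The case against.** The strongest reply has four parts.

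- **The stated alpha belongs to the power calculations.** This is correct. A reader might infer that every outcome, every STI model and the interim look is tested at 0.05, and so that the false-positive rate is far above 5%. The article does not say that.
- **The interim analysis.** Data monitoring says the board will "evaluate findings in an interim analysis of the data to determine if the RCT should continue or be stopped". It gives no timing, outcome or threshold. Boundaries commonly sit in an analysis plan or board charter, so their absence from an article is no finding. Any inflation figure for that look would rest on assumptions the article does not supply, and none is claimed here.
- **The 10% to 14% depends on an any-of-three success rule.** This is also correct, and the rule is not stated. It is not excluded either.
- **The sample size section does mention PrEP and HTC uptake, and choosing a lead model is ordinary analysis-plan work.** Both points narrow the concern. The wording conflict is confined to one phrase and one time horizon, and the model question alone would be minor.

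What survives is that one section names three primary outcomes at 6 months and another names one over 12 months. That is a contradiction in the text, and a further document cannot resolve it without overruling one of them.

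**Conclusion.** The point holds in this limited form. The article contradicts itself on the number of primary outcomes and on the time point of the STI outcome, and its sizing uses 0.05 without division. If success on any one of three outcomes counts, familywise error is 14.3% under independence and about 9.8% to 13.6% at correlations of 0.8 to 0.3, two to three times the nominal level. Under an all-must-succeed or STI-only rule there is no such inflation. The deciding 6-month STI test is not identified.

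The power claim for STI depends on the resolution: under a Bonferroni split it would not hold at 20% incidence on either reading of that figure. The documents do not support saying that the trial's error rate is in fact far above 5%.

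**What to change.** 1. Reconcile the Abstract, Study objectives and Primary outcomes with the Sample size calculation on the number of primary outcomes and their time point.
2. State the success rule and choose one of two routes:
   - keep three primary outcomes with familywise control at 0.05, for example Holm; or
   - name STI incidence as the single primary outcome, and test HTC and PrEP uptake afterwards in a fixed sequence.
3. Name one analysis as primary for STI at 6 months and label the others supportive.
4. Restate power for that outcome, at that time point and alpha, and say whether 20% to 30% is overall or control-arm incidence.

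**Cost.** The change is to the protocol, analysis plan and registry entry, with no new data collection. The first route gives less favourable stated power for STI. The Bonferroni figures above are the floor for Holm, which tests STI at a higher level once another outcome has been rejected. The second route keeps the full 0.05 for STI, but HTC and PrEP uptake lose stand-alone primary status and could not be claimed in the sequence if STI misses. Since raising uptake is a stated aim of the trial, that choice belongs to the investigators; either route would resolve the point.

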**Discussion:**

Primary prevention remains the most viable strategy to stem new STI and HIV transmissions. HIV and STI disparities go beyond individual level factors, and prevention packages that include supportive relationships (e.g., FC) may produce greater reductions in HIV-risk, improve HTC and PrEP uptake, and increase linkage, retention, and adherence to care. Reducing new HIV and STI infections among South African AGYW is global public health priority.

**Trial registration:**

ClinicalTrials.gov Number NCT04758390, accepted 02/16/2021.

## Background

South Africa (SA) is home to the largest number of people living with HIV worldwide, [1, 2] but within-population differences exist [2–4]. HIV rates are higher among women than men, [2, 3] adolescent girls and young women (AGYW) acquire HIV at twice the rate and seroconvert on average 5–7 years earlier than male peers, [2] and AIDS is the second leading cause of death among adolescents [5]. Moreover, AGYW account for over 67% of new HIV infections, [6] but only 15% know their status [7]. Women’s HIV disparities are explained by a multiplicity of social and structural inequities that shape and constrain HIV-risk behaviors and continue to drive incident infections in SA [8–13]. Hence, multilevel prevention packages that are tailored to the local epidemiology and cultural context are likely to achieve and sustain maximum reductions in AGYW HIV-risk [14–21].

Families are a relatively untapped resource in SA’s HIV prevention efforts. Yet, families are uniquely positioned to support prevention, because they are the first socialization experience for adolescent sexual and reproductive health. Mothers and other important female caregivers (FC) (e.g., aunts, cousins) play a central role in AGYW’s sexual behavior and development, and can be effective partners in reducing sexual risk while promoting new biomedical technologies like PrEP and HIV testing and counseling (HTC) [22, 23]. Research that optimizes uptake and adherence to PrEP and HTC in women [24] will facilitate more equitable access to all HIV scientific advances. Research in the US indicates maternal warmth and attachment, close family relationships, parental involvement and support, and positive parenting predict consistent condom use, less exposure to HIV-risk situations, and later sexual debut among adolescents [25–29]. Likewise, mother-daughter communication that is open, receptive, and comfortable is associated with less risky sexual behavior in the US [26, 30–37] and in Africa [38–43].

South African FC may serve as a catalyst for AGYW change. Despite noting parents as the best source of information about sex and general receptivity to such discussions, only 20% of SA youth receive information about sex from their parents, and almost 50% of girls report that they could not openly discuss sexuality with their parents [44, 45]. Likewise, African mothers report needing and wanting accurate knowledge to discuss sex with their children [46]. Capitalizing on the FC-AGYW relationship, improving the quality of FC-AGYW conversations about sexual and reproductive health, teaching FC to use accurate information, and challenging cultural taboos that inhibit communication about sex [47] may alter the current HIV-trajectory for SA AGYW. Notably, AGYW may also be change agents for their FC who want to be positive role models for AGYW. In the process of promoting AGYW sexual and reproductive health, FC may change their own behavior (including HTC and PrEP uptake), thereby reducing their own risk for HIV.

IMARA is an evidence-supported mother-daughter (“mother” refers to any female caregiver) program based on the Social Personal framework [48] and derived from three established interventions: SISTA [49–53] and SiHLE [54] for African American women and girls respectively, and Project STYLE for teens and families in mental health care [55]. SISTA and SiHLE address the importance of relationship power and gender dynamics as drivers of HIV risk behavior. This is critical for the South African context where AGYW’s first and ongoing sexual partner is typically an older male, [56] and AGYW with older partners are four times more likely to test positive for a sexually-transmitted infection (STI), [57] report transactional sex, [57] and have high HIV infection rates [58]. In addition, gender-based violence (GBV) among SA AGYW is higher than in every other region in sub-Saharan Africa, [44, 59, 60] and is related to high rates of STI [61] and HIV-risk, [62–64] and impedes women’s ability to receive HTC, link to treatment, and adhere to PrEP [65–67]. Project STYLE emphasizes parent-teen relationships and communication as protective against HIV and STI risk. A recent efficacy study of IMARA in the US [68] revealed a 43% reduction in incident STI infections at 1-year follow-up among 14–18 year-old African American girls who received IMARA compared to a time-matched health promotion program (*p* = .011).

Adaptation of IMARA to the South African context is important to ensure acceptability and uptake. Added content related to HTC and PrEP, two essential strategies to comprehensive HIV prevention, [69–74] will equip AGYW and FC with greater control and agency over their sexual lives [75]. Moreover, IMARA could provide a novel approach to reduce AGYW STI and HIV-risk and improve HTC and PrEP awareness, acceptability, and uptake (where appropriate) for FC and AGYW. Finally, rigorous cost evaluations of HIV and STI prevention packages are sorely needed to optimize the use of available resources. Establishing the cost-effectiveness (CE) of HIV prevention packages is essential if they are to be sustained [76, 77].

In sum, SA AGYW have not benefitted equally from gains in the HIV epidemic. The unrelenting disparity of new infections in this group [78] requires an expansion of prevention options within the SA context [79]. Focusing on vulnerable populations and high-incidence locations, i.e., SA AGYW, will realize the greatest benefits in altering epidemiological trajectories [80]. While changing behavior can reduce HIV and STI acquisition, [11] research on evidence-based interventions with strong evaluation designs is lacking for AGYW, especially those capitalizing on the strengths and assets of families.

### Study objectives

The purpose of this study is to test the effectiveness and cost-effectiveness of a culturally-tailored, evidence-based, HIV/STI prevention program for SA AGYW and FC. We will randomly assign 525 AGYW-FC dyads to IMARA-SA (*n* = 263) or a family-based health promotion (HP) program (*n* = 262) matched in time and intensity and compare participants on incident STI, and HTC and PrEP uptake at 6 months. Secondary objectives are to assess intervention effects on the primary outcomes at 12 months, reported non-condom use, number of partners, HIV incidence, and adherence to ART/PrEP. We will also evaluate the costs and CE of IMARA with respect to the acquisition of STI and HIV where possible, considering power limitations.

## Methods

### Design

This is an individually randomized controlled trial (RCT) of IMARA for 15–19 year-old Black South African AGYW and their FC. AGYW-FC dyads will be randomized to IMARA-SA versus a family-based HP program. All participants will complete baseline, 6-, and 12-month follow-up assessments via audio computerized assisted self-interview technology (ACASI) and provide urine to screen for three sexually transmitted infections (STI). All participants will also be offered HTC and PrEP, and where appropriate (e.g., if HIV/STI positive), will receive free care at the on-site adolescent-friendly reproductive health clinic at the Desmond Tutu Health Foundation (DTHF) and referral to public clinics.

### Identification and recruitment of participants

The study will take place in Phillippi and the surrounding townships including Nyanga, Gugulethu and Khayelitsha, located in the Cape Town metropolitan. These areas are densely populated, have a high HIV burden, and are poorly resourced. Recruitment strategies include street outreach, word-of-mouth referrals, flyers, and clinic-based contacts by study personnel. The majority of the residents are Black and mixed race. We will enroll AGYW and a FC, defined as an important and influential female in AGYW’s life (e.g., mother, aunt). AGYW will be: a) Black or mixed race; b) 15–19 years-old; c) residing in Phillipi and the surrounding areas who d) speak Xhosa, English, or a combination, as these are the primary regional languages. AGYW may or may not be sexually active, and information about AGYW sexual activity will not be shared with FC. FC will be: a) selected by the AGYW and agreed upon by the legal guardian; b) 24 years or older; c) living with or in daily contact with the AGYW; and d) a speaker of Xhosa and/or English. We will include HIV-infected and uninfected FC and AGYW, and AGYW or FC who become HIV+ and/or pregnant during the study may continue to participate. AGYW and FC must agree to participate as a dyad, but AGYW refusal will supersede FC consent. All participants, regardless of randomization status, will be followed for 12 months with visits conducted at 6 and 12-month intervals (Fig. 1).

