#### Description of the interventions: Informed Motivated Aware and Responsible Adolescents and adults- South Africa (IMARA-SA)

The IMARA curriculum was subject to a comprehensive and systematic adaptation process prior to this RCT. The details of the adaptation process are presented elsewhere [81]. Separate FC and AGYW groups will run simultaneously, cover parallel content, and address individual, social, and structural drivers of HIV-risk (Table 1). Joint activities are designed to enhance FC credibility as a resource for HIV/STI prevention and facilitate practice of new communication skills. Additional activities will address conflict negotiation, assertive communication, and strengthening the AGYW-FC relationship. Interventionists will use interactive and experiential activities to address key constructs. The group format promotes structural change by building community norms for prevention (e.g., HTC and PrEP uptake) and reducing HIV stigma. IMARA-SA’s goals and motto emphasize strong FC-AGYW relationships, sisterhood, empowerment, and motivation for HIV/STI prevention, and build group cohesion. FC and AGYW will sign a pact to confirm commitment to the program. At the end of session 1, participants will receive homework to complete for session 2. Woven throughout IMARA-SA is the impact of mental health, gender-based violence, and alcohol and drug use on HIV-risk.

**Table 1 Tab1:** IMARA-SA Curriculum

Theory	Selected IMARA-SA Activities
Individual Factors	
Knowledge, attitudes, beliefs, skills about HIV, STI, PrEP, HTC	Facts of HIV/AIDS/STI/PrEP/HTC; Prevalence for adolescent girls and young women; PrEP education video; Perceived vulnerability; Personal risk triggers (e.g., people, places, feelings) and risk plans; Demonstrate and practice condom use; De-mystifying HIV testing; Importance of regular HTC and PrEP where appropriate to risk behavior.
Mental health	Destigmatize mental health; Links between mental health problems and HIV-risk behavior; Recognize how feelings trigger risk taking; Teach healthy coping strategies; Recognize the value of the body; Substance use and risk taking; Referrals for counseling
Social Factors	

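### Girls are enrolled whether or not they are sexually active, but adjustment for sexual activity is left to a balance test and the population behind the 20–30% STI incidence is not named

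*Protocol article*

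**What the plan says.** All references are to the protocol article.

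- **Identification and recruitment of participants:** "AGYW may or may not be sexually active, and information about AGYW sexual activity will not be shared with FC". Sexual activity is not an entry criterion.
- **Abstract, Methods:** "Primary outcomes are AGYW STI incidence, HTC uptake, and PrEP uptake at 6 months". The section Primary outcomes defines the STI outcome as three infections: "At 6-month follow-up, we will examine AGYW STI incidence (gonorrhea, chlamydia, and trichomoniasis), PrEP uptake and 1-month supply of medication, and HTC uptake".
- **Design:** "All participants will also be offered HTC and PrEP". PrEP is thus open to every participant.
- **Table 1 (IMARA-SA curriculum):** one taught item is "Importance of regular HTC and PrEP where appropriate to risk behavior", so the programme links PrEP to risk.
- **Randomization:** each girl draws a coloured paper from a hat after the baseline assessment, 1:1, with no strata described.
- **Statistical analysis:** models adjust for the baseline value of the outcome, for confounders that are not named, and for predictors on which the arms are found to differ at baseline, judged by chi-square, t or Wilcoxon tests. Treatment-by-covariate interactions are planned, with mental health and substance use as examples.
- **Sample size calculation:** "we will have ≥80% power to detect hazard ratios ≤0.5 for STI incidence ranging from 20 to 30%, even with 25% attrition". The rates run over 12 months and come from a named earlier study. The text does not describe that study's participants, and it gives no expected share of sexually active girls.

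**The concern.** Gonorrhea, chlamydia and trichomoniasis depend on sexual exposure, so a girl who stays inactive throughout follow-up contributes almost no STI events in either arm. She is also less likely to take PrEP if it is presented as a matter of risk. Sexual activity at baseline should therefore be one of the strongest predictors of two of the three primary outcomes.

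Two consequences follow. First, whether the models use this predictor depends on a significance test of baseline balance, or on a later choice of confounders. A strong prognostic variable is best fixed in advance, because adjusting for it improves precision and removes the effect of chance imbalance whether or not a test flags it. Second, the power statement can be matched to the eligibility rule only if the reader knows whose incidence the 20–30% is. If it is a rate among active girls, the enrolled mix will produce fewer events than planned.

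**Working it through.** **Inputs from the article:** 525 dyads, 1:1; 25% attrition, so 525 × 0.75 = 393.75 followed (about 394, or 196.875 per arm); two-sided alpha 0.05; hazard ratio (HR) 0.5; 12-month incidence 20–30%.

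**Assumed, not in the article:** the share s of girls who are sexually active (70% and 50% shown), and no STI events among the others.

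**Formula** (Schoenfeld): power = Φ(√D / 2 × ln 2 − 1.96), where D is the total number of events. For 80% power, D = 4 × (1.96 + 0.8416)² / (ln 2)² = 65.4, so 66 events.

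**Step 1. Reproduce the plan's figure.** Take 20–30% as the overall rate in everyone followed.
- 20%: D = 393.75 × 0.20 = 78.8; power = Φ(3.08 − 1.96) = 86.8%.
- 30%: D = 393.75 × 0.30 = 118.1; power = 96.5%.

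The stated figure of at least 80% is reproduced. If 20–30% is instead the control-arm rate, D = 196.875 × [p + 1 − (1 − p)^0.5]. This gives 60.2 events and 76.7% at p = 0.20, and 91.2 events and 91.2% at p = 0.30. On that reading the low end misses 80% even with every girl active, so part of any shortfall there is not due to inactive girls.

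**Step 2. Suppose 20–30% applies only to active girls.** On the overall-rate reading, D is multiplied by s. On the control-rate reading, p = s × incidence.

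| Share active | Overall-rate reading: events | Power | Control-rate reading: events | Power |
|---|---|---|---|---|
| 70% | 55.1 to 82.7 | 73.0% to 88.3% | 41.9 to 63.2 | 61% to 79% |
| 50% | 39.4 to 59.1 | 58.5% to 75.9% | 29.8 to 44.9 | 47% to 64% |

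On the overall-rate reading, power falls below 80% when s is under 66 / 78.75 = 0.84 at 20% incidence, 66 / 98.4 = 0.67 at 25%, and 66 / 118.1 = 0.56 at 30%.

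**Step 3. Suppose 20–30% applies to all enrolled girls.** Step 1 stands unchanged. The implied incidence among active girls is then 20/0.7 to 30/0.7, or 29–43%, at s = 0.7, and 40–60% at s = 0.5. The sponsor can check these against its source.

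**Step 4. What inactive girls do to the STI effect.** With 20% control-arm incidence among active girls and HR 0.5, the intervention-arm risk among them is 1 − 0.8^0.5 = 10.6%.
- Relative risk in the whole cohort: (s × 0.1056) / (s × 0.20) = 0.53 for any s. The share cancels, and for the HR it cancels to a close approximation at these rates.
- Absolute difference: s × 9.4 points, so 9.4 points with all active, 6.6 at s = 0.7 and 4.7 at s = 0.5.

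**Step 5. Chance imbalance in s.** With 263 versus 262 girls, the standard deviation of the between-arm difference is √[s(1 − s)(1/263 + 1/262)], or 4.0 points at s = 0.7 and 4.4 at s = 0.5. A 5% test flags only differences beyond about 1.96 times that, 7.8 to 8.6 points. An unflagged 8-point gap at s = 0.5 would shift the STI comparison by about 8 × 0.20 = 1.6 to 8 × 0.30 = 2.4 points.

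The article gives no planning figure for PrEP uptake by sexual activity, so no size is attached to that outcome.

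**The case against.** The case against has real force.

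- **Inactive girls can have the events.** A reader might infer that the STI and PrEP outcomes are undefined for them. The documents do not support this. PrEP is offered to every participant, and a girl who is inactive at enrolment may become active during 12 months. The supportable claim is fewer STI events and probably lower PrEP uptake. This objection stands.
- **Bias toward no effect.** A reader might infer that the STI hazard ratio or relative risk is diluted. Step 4 shows that it is not. This stands too.
- **Underpowering is not shown.** Neither the share active nor the meaning of 20–30% can be read from the article, and the rate may already describe a mixed cohort. This stands, so the power loss can be stated only conditionally and on both readings of the rate.
- **A null result would still be interpretable.** Sexual behaviour is collected at 6 and 12 months, so the exposed share and the event rate will be visible. This stands.
- **Broad enrolment is legitimate** for a prevention programme. The eligibility rule is not the defect.
- **Adjustment and interactions are already planned, and subgroup detail may sit in an analysis plan that is not shown.** This stands only in part. The absence of a named subgroup is no finding in itself. But the article does state an adjustment rule, and that rule brings in sexual activity only through a balance test or an unspecified choice. Adjusting for baseline STI does not replace it, because a negative test does not separate active from inactive girls.
- **Stratifying the draw** might seem the natural remedy. It would need the self-interview answers at the moment of allocation and could reveal to the caregiver what the article says will not be shared. It is not recommended here.

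**Conclusion.** The point holds in a limited form. The article leaves a strong predictor of the STI outcome, and probably of PrEP uptake, to a test-driven adjustment rule. It also gives a planning incidence without saying whose incidence it is.

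If the 20–30% covers all enrolled girls, the stated power stands. If it covers only active girls, the claim of at least 80% fails across the whole incidence range at 50% active. At 70% active it fails at the 20% end on the overall-rate reading, and across the range on the control-rate reading. These results assume the share active and no STI events among the other girls; girls who become active would soften the loss. They use the plan's 12-month horizon; how that fits a 6-month primary time point is a separate question.

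The documents do not support the stronger conclusions that the trial is underpowered or that its eligibility rule is wrong. The change is worth making because it costs almost nothing and improves on the stated rule whichever reading is true.

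**What to change.** Keep the eligibility rule and the allocation method.

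1. **Statistical analysis:** name sexual activity reported at the baseline self-interview (yes/no) as a fixed covariate in the STI and PrEP models, whatever the balance tests show. Baseline collection is implied rather than stated: every participant completes a baseline self-interview, sexual behaviour is a secondary outcome, and the models adjust for outcomes at baseline. The text should confirm it.
2. **Statistical analysis:** pre-specify the STI and PrEP comparisons in girls sexually active at baseline as a supporting analysis beside the all-randomized result. The subgroup is defined before allocation, so the comparison remains a randomized one.
3. **Sample size calculation:** state whether 20–30% refers to all enrolled or to sexually active girls, and whether it is an overall or a control-arm rate. If it refers to active girls, give the expected share active and restate the power for that mix.

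The cost is a few sentences, one more reported analysis and possibly a less favourable stated power. If baseline sexual activity is collected as implied, no new participants or data are needed.
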